## Abstract

**Background:**

Post-stroke insomnia (PSI) is one of the most common and difficult-to-treat complications following stroke, with a prevalence exceeding 50%, and is an independent risk factor for stroke recurrence and secondary anxiety and depressive disorders. Current first-line strategies, namely sedative-hypnotics and cognitive behavioral therapy for insomnia, are constrained by the risks of tolerance, dependence, and cognitive side effects, as well as by limited medical resources and poor patient adherence. Transcutaneous auricular vagus nerve stimulation (taVNS), a non-invasive neuromodulation technique, has demonstrated therapeutic potential in primary insomnia and post-stroke depression. However, evidence for taVNS in PSI remains limited to a few isolated case reports; high-quality randomized controlled trials are lacking, and its underlying central nervous system mechanisms have not been characterized. This protocol is designed to address these gaps.

**Methods/design:**

This single-blind randomized controlled trial will enroll 48 patients with PSI, randomly assigned in a 1:1 ratio to a taVNS group or a sham-taVNS group. Both groups will receive the assigned intervention once daily, five days per week, for four weeks, in addition to standard post-stroke basic treatment. The primary outcomes are multimodal magnetic resonance imaging (MRI) indicators acquired before and after the 4-week intervention, including resting-state functional MRI (amplitude of low-frequency fluctuation, fractional amplitude of low-frequency fluctuation, regional homogeneity, and functional connectivity), three-dimensional T1-weighted structural metrics (gray matter volume, cortical thickness, and cortical surface area), and arterial-spin-labeling cerebral blood flow. The secondary outcomes are clinical efficacy scales, namely the Pittsburgh Sleep Quality Index, the National Institutes of Health Stroke Scale, the Activities of Daily Living scale, the 17-item Hamilton Depression Rating Scale, and the 14-item Hamilton Anxiety Rating Scale, assessed at baseline, week 2, and week 4. Between- and within-group differences will be examined using two-sample and paired t-tests with Gaussian random field correction for imaging data and repeated-measures analysis of variance for clinical data, and Pearson or Spearman correlation analyses will relate neuroimaging changes to clinical improvement.

**Discussion:**

By integrating brain function, brain structure, and cerebral perfusion through multimodal MRI, this study aims to evaluate the clinical efficacy of taVNS in patients with PSI and to elucidate its underlying central nervous system mechanisms. The main limitations are a relatively small sample size and a single-blind design, which may limit the generalizability of the findings and introduce a degree of implementation bias. Nevertheless, the findings will provide evidence-based support for the clinical application of taVNS in PSI and lay the foundation for the development of individualized neuromodulation strategies for post-stroke sleep disorders.

**Clinical trial registration:**

http://itmctr.ccebtcm.org.cn/, identifier ITMCTR2025002545.

## Introduction

Post-Stroke Insomnia (PSI) is one of the highly prevalent and intractable complications following stroke, with a prevalence rate of over 50% (1). Recent meta-analyses have further underscored the magnitude of this problem. A pooled analysis of 26 studies comprising nearly 500,000 stroke patients estimated the prevalence of post-stroke insomnia at approximately 47%, with a comparable rate of 47.21% in patients with ischemic stroke or transient ischemic attack (2). Consistently, a meta-analysis based on the Pittsburgh Sleep Quality Index reported that about 55% of stroke survivors experience poor sleep quality, with a pooled mean score of 8.12 (3). These converging estimates confirm that PSI affects roughly half of stroke survivors, far exceeding the prevalence of insomnia in the general population. Its clinical features mainly manifest as difficulty falling asleep, difficulty maintaining sleep, and circadian rhythm disruption (4). Persistent sleep deprivation not only severely reduces patients’ subjective sleep quality but also significantly impairs their cognitive function and daytime social function (5). Crucially, PSI has been identified as an independent risk factor for stroke recurrence and secondary anxiety disorders (6). Beyond its direct effects on sleep, PSI delays neurological and motor rehabilitation, prolongs hospitalization, increases caregiver burden, and is associated with poorer long-term functional recovery, thereby imposing a substantial clinical and socioeconomic burden. Therefore, in-depth exploration of effective intervention strategies for PSI holds significant clinical importance.

Current therapeutic strategies for PSI include pharmacological interventions and Cognitive Behavioral Therapy for Insomnia (CBT-I) (7). However, their clinical limitations are becoming increasingly evident. Most sedative-hypnotics not only carry risks of tolerance and dependence but may also exacerbate cognitive impairment and increase the risk of falls in stroke patients, thereby adversely affecting prognosis (8). Although CBT-I is recommended by clinical guidelines, its application is hindered by a lack of medical resources and high implementation barriers, resulting in poor patient adherence and an inability to meet the substantial clinical demand (9). Therefore, developing a novel non-pharmacological intervention that is both safe and convenient has emerged as a critical issue requiring urgent resolution in this field.

Transcutaneous auricular vagus nerve stimulation (taVNS) is an emerging non-invasive neuromodulation technique (10). Compared to traditional invasive Vagus Nerve Stimulation (iVNS), taVNS avoids surgical trauma and associated risks, offering higher safety and tolerability (11). Previous studies have confirmed the efficacy of taVNS in treating conditions such as depression (12, 13) and epilepsy (14). In the field of sleep and stroke complications, our team’s prior research has found that taVNS can effectively treat primary insomnia (15–17). Additionally, existing literature supports its role in improving post-stroke depression (18). However, research on taVNS for the treatment of PSI is still in its infancy, with only a few case reports suggesting its potential clinical efficacy (19). There remains a lack of high-quality Randomized Controlled Trials (RCTs) to provide robust evidence-based medical support. Three core gaps therefore remain: the efficacy of taVNS for PSI has not been established in adequately powered, sham-controlled trials; its therapeutic effects have not been evaluated against the multidimensional neuropathology that characterizes PSI; and the central nervous system mechanisms through which taVNS might act are still unknown.

The maintenance of the sleep-wake cycle depends on the dynamic balance at the whole-brain level, involving the precise regulation of specific neural circuits such as the thalamo-cortical loop and the reticular formation of the brainstem (20). After a stroke, ischemic injury directly disrupts these critical neuroanatomical structures and neurotransmitter pathways, leading to an imbalance between sleep drive and the arousal system (21). In recent years, with the rapid development of neuroimaging, multimodal Magnetic Resonance Imaging (MRI) technology has become a key tool for unraveling the complex neuropathological mechanisms of PSI. High-resolution T1-weighted imaging (3D-T1WI) serves as a cornerstone for assessing the integrity of brain microstructure. Techniques such as Voxel-Based Morphometry (VBM) and Surface-Based Morphometry (SBM) enable the precise quantification of key morphological indicators, including Gray Matter Volume (GMV), cortical thickness, and cortical surface area (22, 23). Previous studies have shown that chronic sleep deprivation not only leads to gray matter atrophy in brain regions related to cognition and emotion, such as the hippocampus, prefrontal cortex, and anterior cingulate cortex, but also induces widespread changes in the surface area of the sensorimotor cortex (24, 25). In PSI, these neurodegenerative changes secondary to insomnia, when superimposed on the primary stroke lesion, constitute the anatomical basis for the impeded recovery of neurological function in patients.

As an effective tool for investigating spontaneous neuronal activity by monitoring fluctuations in blood oxygen levels, resting-state functional MRI (rs-fMRI) helps assess the spontaneous evolution of Blood Oxygen Level-Dependent (BOLD) signals and abnormalities in functional connectivity within core brain regions regulating “emotion-arousal” in patients with PSI (26). Recent fMRI studies reveal that PSI is characterized by multi-dimensional spontaneous activity abnormalities, specifically within the visual processing cortex, sensorimotor cortex, and Default Mode Network (DMN) nodes (26). Furthermore, Arterial Spin Labeling (ASL) provides non-invasive, contrast-free quantification of Cerebral Blood Flow (CBF) (27). ASL effectively captures hypoperfusion in ischemic areas and sleep-related brain regions, thereby reflecting the degree of impairment in neurovascular coupling function (28).

Taken together, the pathophysiology of PSI can be conceptualized as a multidimensional process spanning structural damage, functional disruption, and hemodynamic abnormality. This framework provides a clear rationale for taVNS. As a “bottom-up” intervention, taVNS delivers afferent signals through the auricular branch of the vagus nerve to the nucleus tractus solitarius, which in turn projects to the locus coeruleus, thalamus, and limbic and prefrontal regions, that is, the same arousal- and emotion-regulating circuits that are structurally, functionally, and hemodynamically compromised in PSI. taVNS therefore has the potential to act simultaneously on all three of these dimensions, yet this possibility has not been tested. Accordingly, this study adopts a randomized controlled design that integrates 3D-T1WI structural imaging, BOLD-fMRI, and ASL perfusion to evaluate the clinical efficacy of taVNS in PSI and to characterize its effects across brain structure, neural function, and cerebral perfusion. By further examining the cumulative effects of a 4-week intervention, the study aims to clarify how taVNS drives neuroplastic remodeling and to provide a robust theoretical basis for precise clinical intervention in PSI.

## Methods

### Study design

This is a prospective, randomized controlled clinical trial. A total of 48 patients with PSI will be screened according to strict inclusion and exclusion criteria. The protocol has been registered with the International Traditional Medicine Clinical Trial Registry (ITMCTR2025002545) and strictly follows the principles of the Declaration of Helsinki. It has been approved by the Medical Ethics Committee of Beijing Hospital of Traditional Chinese Medicine Shunyi Hospital (2025SYKY-04-03). All participants or their legal guardians are required to sign a written informed consent form prior to enrollment. **Figure 1** provides the detailed information of the study design.

**Figure 1 f1:**
[figure not shown]
Flowchart of the trial. Clinical outcome assessments are conducted at three time points: baseline (Week 0), 2-week evaluation (Week 2), and 4-week evaluation (Week 4). PSI, Post-stroke insomnia; taVNS, transcutaneous auricular vagus nerve stimulation; MRI, Magnetic Resonance Imaging.

### Inclusion criteria

(1) Confirmed by MRI and meeting the diagnostic criteria for ischemic cerebrovascular disease; (2) Aged between 40 and 80 years, regardless of gender; (3) Insomnia first occurring more than 2 weeks after acute stroke, with no prior history of insomnia; (4) Pittsburgh Sleep Quality Index (PSQI) score > 7; (5) Conscious and able to cooperate with all scale assessments; (6) Voluntary participation in the study, signing the informed consent form, and committing not to participate in other clinical studies during the treatment period.

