### Exclusion criteria

(1) Unstable condition or recurrence of stroke during the treatment period; (2) Severe bleeding tendency, or concurrent failure of vital organs such as the heart, liver, or kidneys; (3) Insomnia caused by other definite etiologies; (4) Comorbid severe mental illness; (5) Currently participating in other clinical trials; (6) Contraindications to MRI; (7) Hemorrhagic stroke patients; (8) History of ear infection or prior vagus nerve surgery.

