### Blinding

To ensure methodological rigor, this trial adopts a single-blind design. Participants will be blinded to group allocation and treated in separate rooms to minimize communication between groups. To assess the effectiveness of the blinding, participants will be asked to guess their group assignment (taVNS group or sham-taVNS group) after the intervention. Due to the specific nature of the taVNS intervention, the therapists cannot be blinded. In contrast, both the outcome assessors and the statistical analysts will remain blinded to the group assignments throughout the study.

Eligible participants will be randomly assigned to the taVNS group or sham-taVNS group in a 1:1 ratio using a computer-generated random sequence. Allocation concealment will be maintained using sequentially numbered, opaque, sealed envelopes prepared by an independent researcher who is not involved in recruitment, intervention, outcome assessment, or data analysis.

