Such integrated analyses are expected to identify specific neuroimaging biomarkers that can not only predict treatment responsiveness but also clarify the central mechanisms through which taVNS exerts its therapeutic effects. For example, the association between enhanced functional connectivity in the DMN and reduced PSQI scores may suggest that taVNS exerts its sleep-promoting effects by modulating large-scale neural networks involved in self-referential processing and arousal regulation (70). Similarly, the correlation between increased cerebral blood flow in the thalamus and prefrontal regions and improved sleep maintenance may indicate that the restoration of neurovascular coupling is one of its key mechanisms of action (71). Building on these prior mechanistic findings, we can make several specific predictions regarding the brain regions most likely to be modulated by taVNS in PSI. At the functional level, given that taVNS has been shown to normalize spontaneous activity and to enhance connectivity within the default mode network, thalamus, and prefrontal cortex in primary insomnia and depression (17, 40, 70), we anticipate that the taVNS group will show increased ALFF/fALFF and ReHo in the prefrontal cortex and precuneus, together with strengthened thalamo-cortical and intra-DMN functional connectivity. At the structural level, because chronic sleep deprivation is associated with gray matter atrophy in the hippocampus, prefrontal cortex, and anterior cingulate cortex (24, 25), a 4-week intervention may produce measurable increases, or attenuated loss, of gray matter volume and cortical thickness in these emotion- and cognition-related regions. At the perfusion level, taVNS is expected to increase cerebral blood flow in the thalamus and prefrontal cortex, reflecting restored neurovascular coupling in hypoperfused, sleep-regulating areas. We further hypothesize that these regional changes will correlate with clinical improvement, such that greater enhancement of prefrontal-thalamic function and perfusion is accompanied by larger reductions in PSQI and HAMD/HAMA scores. Specifying these candidate regions and directional hypotheses in advance strengthens the forward-looking value of the protocol and provides concrete, testable targets for the planned analyses.

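### Lesion site and side enter neither the allocation nor the between-group imaging tests, leaving avoidable variance and exposure to chance imbalance in a 48-patient stroke trial

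*Protocol article*

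**What the plan says.** All references are to the protocol article.

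- **Eligibility.** Inclusion criterion 1 reads "Confirmed by MRI and meeting the diagnostic criteria for ischemic cerebrovascular disease". The only restriction by stroke type in the Exclusion criteria is "Hemorrhagic stroke patients". Unstable or recurrent stroke is also excluded, but no lesion is excluded by site, side or size. On timing, the Inclusion criteria require "Insomnia first occurring more than 2 weeks after acute stroke, with no prior history of insomnia", with no upper limit on time since stroke.
- **Allocation.** The randomisation paragraph under Blinding has patients "randomly assigned to the taVNS group or sham-taVNS group in a 1:1 ratio using a computer-generated random sequence". It names no stratification or minimisation factor.
- **Analysis.** Imaging data analysis fixes two-sample and paired t-tests for the rs-fMRI, structural and ASL measures. The only covariates named are time-series nuisance signals (head motion, white matter, CSF). Clinical data analysis has no lesion term either.
- **Mechanism.** The Introduction says taVNS "delivers afferent signals through the auricular branch of the vagus nerve to the nucleus tractus solitarius", and from there to the locus coeruleus, thalamus, limbic and prefrontal regions. Of the thalamo-cortical loop and brainstem reticular formation, it says that after stroke "ischemic injury directly disrupts these critical neuroanatomical structures and neurotransmitter pathways". The Discussion predicts that "taVNS is expected to increase cerebral blood flow in the thalamus and prefrontal cortex".
- **Limitations.** The list in the Discussion does not mention lesion heterogeneity.

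**The concern.** In a stroke population, lesion location is an obvious source of between-patient variation in brain imaging. Here it also bears on the hypothesis, because the pathway the treatment is said to use overlaps the structures the protocol says stroke damages. Three consequences follow.

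1. **Precision.** If imaging change over 4 weeks depends on lesion side, leaving side out of the model puts that variation into the error term.
2. **The realised comparison.** With 24 per arm and no balancing, the arms can differ by chance in lesion side. A between-arm difference in a lateralised region could then partly reflect that imbalance, and the planned test could not separate the two. Clusters from these tests go further: they define the seeds for functional connectivity and supply the values for the brain-behaviour correlations.
3. **Dilution.** Patients whose infarct involves the relay or target regions may respond less, which would lower the mean difference between arms.

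**Working it through.** **The plan's own figure.** 2 × 24 = 48 agrees with the stated total. Sample size calculation gives no effect size, SD or power (it starts from a recommended minimum of 12 per group), so there is no power figure to reproduce.

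**Inputs from the article.** 24 per arm; 1:1 allocation with no named factor; primary contrast is the between-group difference in change from baseline (Primary outcomes); voxel-level threshold 0.005 for the rs-fMRI, VBM and ASL analyses; two-sided 0.05 for conventional tests.

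**Assumed inputs.** 24 of the 48 lesions are left-sided; all 48 are analysed; the 4-week change at a lateralised region differs between left- and right-lesioned patients by s = 0.5 to 1.0 within-side SD. The documents give none of these.

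**Step 1: variance due to side.** With half the patients on each side, the share is 0.25s² / (1 + 0.25s²).
- s = 0.5: 0.0625 / 1.0625 = 0.059
- s = 1.0: 0.25 / 1.25 = 0.20

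**Step 2: chance of imbalance.** The number X of left-sided lesions in the taVNS arm is hypergeometric (48 patients, 24 left-sided, 24 drawn), and the arms differ by |2X − 24|.
- Difference of 4 or more (X ≤ 10 or X ≥ 14): 0.387
- Difference of 6 or more (X ≤ 9 or X ≥ 15): 0.148
- Difference of 8 or more (X ≤ 8 or X ≥ 16): 0.042

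**Step 3: shift from a 6-patient difference (15 v 9).** The shift is s × 6/24.
- s = 0.5: 0.125 SD
- s = 1.0: 0.25 SD

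For scale, the smallest effect detectable with 80% power at 24 per arm is 0.83 SD at 0.05 and 1.10 SD at 0.005 (noncentral t).

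**Step 4: false-positive rate with no treatment effect** (50,000 simulated trials per row, single-region test).

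| Split, side effect | Plain t-test, 0.05 | Plain t-test, 0.005 | Side as covariate, 0.05 | Side as covariate, 0.005 |
|---|---|---|---|---|
| 15 v 9, 0.5 SD | 0.064 | 0.007 | 0.051 | 0.005 |
| 15 v 9, 1.0 SD | 0.091 | 0.011 | 0.050 | 0.005 |
| 12 v 12, 1.0 SD | 0.027 | 0.002 | 0.049 | 0.005 |

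Averaged over all allocations, the plain t-test keeps its level: 0.048 to 0.050 at 0.05 and 0.004 to 0.005 at 0.005, for s = 0.5 to 1.0. The last table row shows the other side of this. When side happens to be balanced, the plain test is conservative because side variance stays in its error term. Cluster-level error was not simulated.

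**Step 5: dilution, illustration only.** If a share f of patients showed no effect at all, the mean effect would fall from d to (1 − f)d. At an assumed d = 0.8, 24 per arm and 0.05, power would be 0.77 for f = 0, 0.67 for f = 0.1 and 0.56 for f = 0.2. Neither d nor f comes from the documents, and complete non-response is the extreme case.

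**The case against.** - **Randomisation already protects the test.** This is right on average, as step 4 shows. A reader might infer that side imbalance biases the trial or would readily produce a false taVNS effect. The documents and the arithmetic do not support that: the imbalance arises by chance, and even in the 15 v 9 case the inflation is modest. What remains is a risk to the one realised comparison, plus lost precision.
- **Change scores remove lesion effects.** Fixed effects do cancel. Only a side-dependent 4-week change matters, and no passage says that recovery is concentrated in the lesioned hemisphere or gives the predicted regions a laterality. That premise remains an assumption. It is plausible because time since stroke has no upper limit, all patients receive rehabilitation, and the Interventions section ties the 4-week course to the timescale of post-stroke plasticity.
- **Damaged circuits are the target.** A reader might infer that patients with a relay or target infarct cannot respond. The Introduction does not support this: it presents the compromised circuits as the reason to use taVNS. An average effect across all eligible patients is also a legitimate question. A weaker response in some patients is possible, but its size is unknown.
- **Covariates belong in the analysis plan.** Often they do, and a fuller document may exist. But the article states its eligibility and allocation, and it specifies the imaging tests down to smoothing kernels and cluster thresholds. The test it names, a plain two-sample t-test, has no place for a covariate. The point is therefore an improvement to a stated method.

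**Conclusion.** The point holds in a limited form. Lesion site and side are unrestricted, unbalanced in the design as described, and absent from the stated between-group tests, although the protocol's own mechanism makes them relevant. If side shifts the 4-week change by 0.5 to 1.0 SD and half the lesions are left-sided, the plan leaves about 6 to 20% of the variance unexplained. It also runs about a 15% chance of an imbalance of 6 or more patients. At 6, the shift is 0.13 to 0.25 SD, with a conditional false-positive rate of about 0.06 to 0.09 at 0.05, or 0.007 to 0.011 at 0.005. Overall type I error is not inflated. Dilution from relay or target infarcts is possible, but it cannot be sized from the documents. The case for change rests on a useful gain at low cost; the planned test is not invalid.

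**What to change.** 1. Before randomisation, code lesion side and yes/no involvement of brainstem, thalamus and prefrontal cortex from the MRI already required by inclusion criterion 1.
2. Balance allocation on lesion side (left / right / brainstem or bilateral). If that is no longer possible, at least enter side as a covariate in every between-group imaging model, using a general linear model in place of the plain two-sample t-test. If allocation is balanced, keep the covariate as well; otherwise the test is conservative, as the 12 v 12 row shows.
3. Prespecify one sensitivity analysis without participants whose infarct involves regions named in advance: brainstem relay, thalamus or prefrontal cortex. Do not define the excluded set by overlap with observed clusters, because the result would then choose the sample and the set would change with every cluster and measure.

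**Cost.** One coding form, 1 to 2 of the 46 residual degrees of freedom (48 − 2), and one extra analysis in a smaller set. No patient is excluded from the trial. Balancing and covariate adjustment do not remove dilution, and the sensitivity analysis only describes it. Balancing cannot be added once allocation is complete, whereas the covariate and sensitivity analysis can still be fixed before unblinding.

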### Sample size calculation

Currently, no precise method exists for calculating the sample size for acupuncture neuroimaging trials. Based on international reviews, a minimum of 12 cases per group is recommended (29, 30). To account for potential data loss and exclusions, this trial will enroll 24 subjects per group, totaling 48 participants.

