### Interventions

In the taVNS group, a taVNS device will be used (Hwato, SDZ-IIB, Suzhou, China) to stimulate the auricular branch of the vagus nerve distribution area located posterior and inferior to the external auditory meatus, with clear anatomical localization. The stimulation parameters will be as follows (31, 32): (1) dense-sparse waves with a pulse frequency of 4/20 Hz; (2) current intensity of 3–14 mA, individually adjusted according to the patient’s tolerance; (3) stimulation time of 30 min per session. Patients will be placed in a comfortable position. The treatment will be administered once daily, five days per week, for a total of four weeks. These parameters were chosen on the basis of our team’s previous taVNS trials in primary insomnia and depression, in which the same dense-disperse 4/20 Hz waveform and 30-minute daily session produced clinical benefit with good safety and tolerability (15, 31, 32). The auricular branch of the vagus nerve distribution was selected as the stimulation target because this region is densely innervated by vagal afferent fibers, enabling direct, non-invasive activation of the vagal pathway. The current intensity will be individually titrated within the 3–14 mA range to the highest level that evokes a distinct but non-painful tingling sensation, so as to ensure adequate afferent activation while maintaining tolerability and minimizing the risk of adverse effects (10). The 4-week course was set to match the intervention duration shown to be effective in our prior insomnia studies and to align with the typical timescale of post-stroke neuroplastic change.

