### Outcome measures

#### Primary outcomes

The primary outcomes include neuroimaging indicators derived from fMRI, 3D-T1WI, and ASL, specifically: The primary outcome is defined as the change in these multimodal MRI indicators from baseline to the end of the 4-week intervention; the principal comparison is the between-group difference in these changes (taVNS vs. sham-taVNS), with within-group pre-to-post changes assessed as a secondary contrast. The specific indicators are as follows:

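### Time since stroke has no upper limit and is left out of the stated between-group tests; adjusting for it would protect precision at 24 per arm

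*Protocol article*

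**What the plan says.** Inclusion criterion (3) reads "Insomnia first occurring more than 2 weeks after acute stroke, with no prior history of insomnia". It dates the onset of insomnia, not enrolment, so a minimum time from stroke to entry is only implied. No inclusion criterion sets a maximum. The nearest exclusion is "Unstable condition or recurrence of stroke during the treatment period", which concerns stability and recurrence rather than elapsed time. A patient some weeks after stroke and one some years after can both enter.

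On allocation, the Blinding section says patients will be "randomly assigned to the taVNS group or sham-taVNS group in a 1:1 ratio using a computer-generated random sequence". No stratification factor is named. The Sample size calculation section states that "this trial will enroll 24 subjects per group, totaling 48 participants".

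Under Primary outcomes, "the principal comparison is the between-group difference in these changes (taVNS vs. sham-taVNS"), with within-group change as a secondary contrast. Imaging data analysis names two-sample and paired t-tests for each modality. Clinical data analysis names independent and paired t-tests, a rank test for non-normal data, and repeated-measures ANOVA for the three visits. Neither section mentions a covariate.

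Under Interventions, the 4-week course is said to be chosen partly "to align with the typical timescale of post-stroke neuroplastic change".

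**The concern.** The change scores span neurological deficit, daily function, sleep, mood, perfusion, resting activity and cortical structure over 4 weeks, during which everyone also receives rehabilitation. If patients at different distances from their stroke change at different rates without stimulation, time since stroke is prognostic for those scores. Leaving it out of the comparison has two effects:

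- The difference between early and late patients goes into the error term and lowers power.
- In any one trial, an arm that by chance holds more early patients has its mean change shifted. Where several measures share the dependence on time since stroke, they shift together and could resemble a coherent mechanism.

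The trial is small, has no power calculation, and concedes limited power in its Discussion. It has little precision to spare.

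**Working it through.** **The plan's own figure.** 2 × 24 = 48 agrees. The plan starts from "a minimum of 12 cases per group is recommended" and gives no effect size, SD or power. The effect of the omission therefore has to be worked out on assumptions.

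**Inputs.** From the protocol: 24 per arm and two-sided 5% tests. Assumed: half the patients are early; early patients change spontaneously by R within-stratum SDs more than late ones, with R from 0.25 to 1; the true effect is 0.8 SD. On the PSQI, this range of R corresponds to 1 to 3 extra points with an SD of change of 3 to 4 (1/4 = 0.25; 3/3 = 1).

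**Step 1, chance imbalance.** With 24 early patients among 48 and 24 per arm, the number X of early patients in one arm is hypergeometric with mean 12, and the arms differ by 2|X − 12|.

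- Differ by 4 or more (at least 4/24 = 17 percentage points): P(|X − 12| ≥ 2) = 0.387.
- Differ by 6 or more (at least 25 points): P(|X − 12| ≥ 3) = 0.148.

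If the total number of early patients is itself random (each patient early with probability 0.5), the second figure is 0.111.

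**Step 2, shift from a 6-patient imbalance.** Shift = R × 6/24, or 0.0625 to 0.25 SD. In PSQI points this is 1 × 0.25 = 0.25 to 3 × 0.25 = 0.75.

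**Step 3, variance and power of the unadjusted t-test.** Variance factor = 1 + R² × 0.5 × 0.5 = 1 + R²/4. SE of the difference = √(factor × 2/24). Effective standardised effect = 0.8/√factor. Power is from the noncentral t with 24 per arm.

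| R (SD) | Variance factor | SE (SD) | Effective effect | Power |
|---|---|---|---|---|
| 0 | 1.000 | 0.289 | 0.800 | 77% |
| 0.25 | 1.016 | 0.291 | 0.794 | 77% |
| 0.5 | 1.063 | 0.298 | 0.776 | 75% |
| 1 | 1.250 | 0.323 | 0.716 | 68% |

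Simulation (40,000 trials per setting) gave 78%, 75% and 68% for R = 0, 0.5 and 1. With early status as a covariate, simulated power was about 77% at every R, and stratifying as well as adjusting also gave about 77%.

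**Step 4, bias and type I error.** In the same simulation, without adjustment, the mean estimate was 0.00 under no effect and 0.80 under a 0.8 SD effect. Type I error was 5.0 to 5.2% for R from 0 to 1. Among only those trials with an imbalance of 6 or more, the unadjusted false-positive rate was about 6%, 7% and 11% for R = 0.25, 0.5 and 1.

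These figures describe a single summary measure in SD units. They carry over in direction, but not in exact size, to voxel-wise tests with cluster correction.

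**The case against.** The strongest reply is that randomisation already deals with this. A reader might infer that spontaneous recovery is confounded with the taVNS effect in the principal comparison. It is not: the sham arm is concurrent and randomised, recovery is balanced in expectation, and the t-test's standard error already allows for chance imbalance. Step 4 confirms this. The raised error rates in imbalanced trials are conditional and average out to 5%. The within-group paired tests cannot separate natural recovery from stimulation, but they are a secondary contrast, and the covariate proposed here is not a remedy for that.

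A reader might also take the Interventions section as conceding that early patients recover and late ones hardly change. It says only that the course length matches a typical timescale, without comparing patients by time since stroke. The recovery difference is therefore an assumption, least secure for cortical structure and the PSQI. Excluding unstable patients may also remove some of the fastest changers.

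Two further replies have partial force. Stratification may be described in a fuller protocol not shown, so silence on it is not counted here as a defect. The analysis is different: the tests are named, and a two-sample t-test has no place for a covariate. Other factors, such as severity or baseline PSQI, could also be prognostic. That does not remove the case for this one, whose range eligibility leaves open.

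Finally, the effect is modest. A 6-patient imbalance moves the estimate by about 0.2 to 0.8 of a standard error (0.0625/0.291 to 0.25/0.323), and at R = 0.25 the power loss is negligible.

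**Conclusion.** The point holds as a matter of efficiency and chance imbalance, not bias. Time since stroke is unbounded above, and the stated between-group tests ignore it. If half the patients are early and differ in spontaneous change by 0.25 to 1 SD, variance rises by 2 to 25%. Power for a 0.8 SD effect falls by under 1 point at R = 0.25, by about 2 to 3 points at 0.5 and by about 10 at 1. About 15% of trials (11% if the early total is random) would have arms differing by 6 or more early patients. The early share, R and the 0.8 SD effect are all assumptions. The change is worth making because it recovers nearly all of that loss at very small cost.

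**What to change.** Replace the unadjusted between-group tests with linear models of the change scores that contain group and time since stroke, for each imaging measure and each clinical scale. The planned cluster corrections can stay. In the repeated-measures analysis, include the interaction of time since stroke with visit, since a main effect alone leaves the change scores unadjusted. Fix the form of the covariate before unblinding: two levels or a transformed continuous value, because a span from weeks to years may be strongly skewed. Any cut point is for the investigators to choose. The date of stroke is already needed to apply criterion (3).

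The cost is one degree of freedom for a two-level or single-term covariate. If time since stroke turns out not to be prognostic, simulated power moves only from 77.6% to 76.8%.

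If enrolment has not begun, the envelopes may also be prepared in two sets, with permuted blocks within each time-since-stroke level. This adds some handling and little power beyond adjustment, so it is optional. If enrolment has begun, the covariate alone is enough. No change to eligibility is needed for this point.
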